## 1. Acronyms and Abbreviations

|      |                                   |
|------|-----------------------------------|
| ALS  | Advanced life support             |
| BVM  | Bag valve mask                    |
| CPC  | Cerebral performance category     |
| CPR  | Cardiopulmonary resuscitation     |
| EMS  | Emergency medical service         |
| ETI  | Endotracheal intubation           |
| OHCA | Out of hospital cardiac arrest    |
| RCT  | Randomized controlled trial       |
| ROSC | Return of Spontaneous Circulation |
| SGA  | Supraglottic Airway               |

## 2. Trial summary

Overall survival of patients after out-of-hospital cardiac arrest (OHCA) is less than 10% worldwide. Interventions provided by emergency medical system (EMS) before arrival at hospital are of paramount importance to patient outcomes after OHCA. Among those interventions, the pros-and-cons of different prehospital advanced airways, including supraglottic airway (SGA) or endotracheal tube, remained the issue of most under debate. The objective of this study is to determine the comparative effective of endotracheal intubation (ETI) vs SGA after OHCA by conducting a randomized controlled trial (RCT) in Taipei EMS.

In this 3-year successive research plan, we will conduct a prehospital randomized controlled trial to address the following question (in Population-Intervention-Comparison-Outcome style): In adult patients with non-traumatic cause of OHCA resuscitated by emergency medical technician paramedic in the prehospital setting, will receiving ETI cause a better chance of sustained recovery of spontaneous circulation and other survival outcomes like neurologically favorable status, comparing to those who receiving SGA device. To name in short, which was called “SAVE trial”, standing for Supraglottic Airway Versus Endotracheal tube.

According to the previous literature, background data, and previous experience in conducting the very first prehospital RCT in Taiwan and Asia by our research team, we estimated the sample size as 852 patients of OHCA to detect the primary outcome difference, and will take a 34-month period to complete the enrollment. As we know, conducting RCT especially in the prehospital setting is a pain-taking, time-consuming task but it is also a must-be-done to answer the most important question in the prehospital airway management by paramedics for patients with OHCA.

Expected results from this “SAVE trial” can figure out the best strategy of prehospital advanced airway in our own and worldwide EMS with similar configuration, therefore find out the promising chance to improve outcomes of patients with OHCA.

## 3. Background

Resuscitation of out-of-hospital cardiac arrest (OHCA) patients is one of the most important issues in emergency medical service (EMS) care.

During cardiac arrest, the brain will be damaged to varying degrees due to low blood oxygen and circulation. High-quality cardiopulmonary resuscitation (CPR) is vital to

reduce the damage of cardiac arrest. Besides, effective ventilation is the basis to maintain the blood oxygenation in the brain, thereby reducing hypoxia and brain damage, and can increase the possibility of return of spontaneous circulation (ROSC) and the chance of neurologically intact survival. [1, 2]

For cardiac patients, the "chain of survival" emphasized early recognition, early CPR, early defibrillation, early advanced life support and post arrest care. There is no doubt about the benefits of early CPR and defibrillation. [3-5] While the prehospital airway management of OHCA patients remained controversial. The airway management in prehospital settings can be divided into basic and advanced techniques. The basic technique includes bag valve mask (BVM) and the advanced technique includes both supraglottic airway device (SGA) and endotracheal intubation (ETI).

The advantage of advanced airway management is to provide a definite and secure way of oxygen delivery in the first aid of sudden cardiac arrest patients. Compared to BVM, advanced airway management may further reduce the interruption during ambulance transport. Advanced care paramedics in Taiwan were authorized to perform either SGA or ETI in the prehospital setting. While ETI may have some pitfalls like esophageal intubation, CPR interruption and may further influence a patient's outcome. [6-10] Theoretically, the SGA can be established quickly, and some studies have also confirmed that the SGA is better than ETI in resuscitation and can reduce the interruption during CPR. [11] However, such inferences were questioned in the following studies. Compared with SGA, ETI achieved higher sustained ROSC (odds ratio [OR] 1.35; 95% confidence interval [CI] 1.19–1.54) according to the analysis from Cardiac Arrest Registry to Enhance Survival (CARES) registry. [12] A recent meta-analysis included 34,533 ETI patients and 41,116 SGA patients that revealed ETI had statistically significant higher odds of ROSC (OR 1.28, 95% CI 1.05-1.55) compared to SGA, while no RCT exists to compare these two airway interventions, resulting in an overall low quality of evidence. [13]

In summary, previous conclusions were the result of retrospective studies, and there are interference factors that cannot be corrected innately in the research design, such as the airway management techniques of paramedics, the quality of chest compression, different types of airway devices, EMS protocols, etc. Therefore, inconsistent conclusions of previous studies appeared and RCT was the best way to further clarify the effect of prehospital airway management between SGA and ETI.

#### **4. Trial Design**

This trial is a randomized controlled trial and will use cluster randomization with periodic crossover.

##### **4.1. Hypothesis**

The hypothesis of the trial was illustrated by the PICO style, (Population-Intervention-Comparison-Outcome). The non-traumatic OHCA patients (Population) in Taipei city who receive ETI(Intervention) can achieve higher sustained ROSC (Outcome) rate comparing to patients who receive SGA insertion (Comparison).

##### **4.2. Inclusion Criteria: the trial will include patients meeting all of the following conditions**

- Out-of-hospital cardiac arrest
- Non-traumatic etiology
- Age  $\geq 20$  years
- Treat by participating ALS teams' paramedics
- Require advanced airway management

#### **4.3. Exclusion Criteria: the trial will exclude patients meeting one of the following conditions**

- Resuscitation deemed inappropriate: rigor mortis or livor mortis
- Not suitable for ETI: like facial deformity, mouth nearly open
- Not suitable for SGA: like preexisting tracheostomy, known upper airway obstruction with a foreign body, anaphylactic laryngeal edema
- Cardiac arrest during transportation en route
- Family made a do-not-resuscitate request at the scene
- ROSC at the scene and no need for advanced airway
- Paramedic participation in the study second on scene and airway management already been established

#### **4.4. Trial setting**

Paramedics who work in the four ALS teams in Taipei city will be enrolled automatically.

The four ALS teams are staffed by approximately 120 paramedics who are trained and authorized to perform ETI/ SGA insertion and intravenous injections of medications. Paramedics have completed 1,280 hours of training, according to the requirements of the Taiwan Ministry of Health and Welfare.

Taipei City is a metropolitan area with a population around 2.65 million, and up to 3.0 million including the inflow of daytime workers, within its 272-km^2 area. The majority of the population is Taiwanese or Chinese.

#### **4.5. Randomization and blinding**

Four ALS teams will be divided into two randomization clusters. Each cluster is assigned to either ETI or SGA in a biweekly period. The study center will instruct the clusters to alternatively change to either the ETI or SGA according to the sequence random allocation.

To guarantee a balanced case number in the final analysis. The allocation periods of ETI vs. SGA in the fashion of three periods of ETI to two periods of SGA (3:2 ratio), which is based on the baseline first attempt success rates of ETI and SGA in the Taipei EMS system (i.e., the success rate of first attempt: 60% of ETI vs. 90% of SGA).

The blinding of paramedics is not possible due to the airway management devices cannot be concealed.

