#### **4.6. Exposure management**

##### **4.6.1. Intervention group**

The intervention arm of the trial is primary ETI in eligible patients according to inclusion criteria. The endotracheal tube will be inserted via direct laryngoscopy but

not video laryngoscopy. There is no additional training course for paramedics who are involved in this trial.

The confirmation of success ETI is mainly by end-tidal capnographic data and auscultation. Protocol-based single-attempt intubation is also applied.

If the first advanced airway attempt fails, rescue airway management including SGA insertion or BVM ventilation are allowed.

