### **5. Sample size estimation**

The sample size estimation is based on the primary outcome of sustained ROSC. According to previous study conducted in Taipei, sustained ROSC rate was 24.4% for SGA and 30.8 % for ETI. [15]

We estimated to enroll 852 patients to detect the absolute difference of 6.4% between the SGA and ETI group to have 80% power and a two-sided  $\alpha$ -level of 0.05.

Considering the number of OHCA patients treated by the participating ALS teams in Taipei is about 300 patients annually, we expect to have adequate number of patients of the three years study period.

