## **9. Analytic plan**

The statistical analysis methods include descriptive analysis, T-test, Chi-squared test, logistic regression, and propensity score analysis.

For the effect of airway management devices between ETI and SGA, odds ratios and 95% confidence intervals will be calculated. All tests are two-sided, and a p-value  $< 0.05$ , will be considered statistically significant.

The analysis will be done according to both intention-to-treat and as-treated principles, and reported according to the CONSORT guidelines.

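### The 3:2 period ratio equalises expected first-attempt successes, not the case numbers in either planned analysis, so the balance promised in Protocol 4.5 is wrong for ITT and not assured as-treated

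*Protocol*

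**What the plan says.** Protocol section 4.5 groups four ALS teams into two clusters, each assigned to ETI or SGA for two weeks at a time. The schedule is set as follows: "The allocation periods of ETI vs. SGA in the fashion of three periods of ETI to two periods of SGA (3:2 ratio"). Its purpose is given as "To guarantee a balanced case number in the final analysis", and its basis as "the success rate of first attempt: 60% of ETI vs. 90% of SGA".

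Section 9 names the analyses: "The analysis will be done according to both intention-to-treat and as-treated principles". Neither is called primary, and as-treated is not defined.

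If the first ETI attempt fails, section 4.6.1 states that "rescue airway management including SGA insertion or BVM ventilation are allowed". Section 4.6.2 mirrors this for a failed SGA, with ETI or BVM as rescue.

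Section 5 plans on the basis that "sustained ROSC rate was 24.4% for SGA and 30.8 % for ETI", and states: "We estimated to enroll 852 patients to detect the absolute difference of 6.4% between the SGA and ETI group to have 80% power". It gives no allocation ratio.

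**The concern.** An allocation ratio fixes how many patients are assigned to each arm. Here it was derived from success rates, which are known only after assignment. If the ratio balances successes, it cannot also balance assigned patients, and ITT counts every patient by assigned device. The protocol would then claim a design property that its main randomised comparison does not have.

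Three things are at stake:

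- the accuracy of the design statement;
- some precision under ITT, in a sample size section that is silent on the ratio;
- the share of calendar time in which both devices are in use.

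**Working it through.** **Inputs.** Ratio 3:2 and first-attempt success 60% and 90% (section 4.5); N = 852, sustained ROSC 24.4% (SGA) and 30.8% (ETI), two-sided 0.05, 80% power (section 5); rescue rules (4.6.1, 4.6.2). Assumption: equal expected accrual per cluster-period, so that patients split as periods do. The protocol gives no accrual by arm or period.

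**1. The stated sample size.** The usual two-proportion formula (pooled variance under the null, 1:1) gives 765 per arm, 1,530 in total, for 80% power. Across 1:1 and 3:2 and the usual variants, two-sided totals run from 1,524 to 1,668, and one-sided totals from 1,202 to 1,325. None gives 852. That is a separate problem. 852 is used below only as the planned enrolment, and the 60/40 split does not depend on it.

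**2. What 3:2 balances.**

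- Assigned: 852 × 0.6 = 511.2 ETI; 852 × 0.4 = 340.8 SGA.
- First-attempt successes: 511.2 × 0.6 = 306.7 ETI; 340.8 × 0.9 = 306.7 SGA.

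Successes are equal; assigned patients are not.

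**3. Could ITT come out balanced by chance?** If patients arrive independently, the SD of the ETI count is √(852 × 0.6 × 0.4) = 14.3. A 426:426 split lies (511.2 − 426)/14.3 ≈ 6 SD away.

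**4. As-treated.** Classify by the device finally in place, with BVM in neither group. Expected first-attempt failures are 511.2 × 0.4 = 204.5 (ETI) and 340.8 × 0.1 = 34.1 (SGA). Let a share r of failures in both arms be rescued with the other device:

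ETI = 306.7 + 34.1r; SGA = 306.7 + 204.5r.

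| r | ETI | SGA |
|---|---|---|
| 0 | 307 | 307 |
| 0.5 | 324 | 409 |
| 1 | 341 | 511 |

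With a common r, balance holds only at r = 0. If r differs by arm, balance needs the two flows to be equal. As 204.5/34.1 = 6, ETI failures would have to be rescued with SGA at one sixth of the rate at which SGA failures are rescued with ETI. Nothing in the protocol requires either.

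**5. ITT precision.** SE of the risk difference = √[0.244 × 0.756/n(SGA) + 0.308 × 0.692/n(ETI)].

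- 1:1: √(0.184464/426 + 0.213136/426) = 0.03055.
- 3:2: √(0.184464/340.8 + 0.213136/511.2) = 0.03095.
- Ratio 1.013, so SE +1.3%.

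Power = Φ[(0.064 − 1.96 × SE₀)/SE], where SE₀ is the pooled null standard error.

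- 1:1: pooled rate 0.276, SE₀ = 0.03063, power 55.2%.
- 3:2: pooled rate 0.2824, SE₀ = 0.03148, power 53.0%.

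Total N for 80% power is 1,530 at 1:1 and 641 + 962 = 1,603 at 3:2, or 73 more. Section 9.1 reports an odds ratio. On the log scale the variance is (1/0.184464)/n(SGA) + (1/0.213136)/n(ETI): 0.02374 at 1:1 and 0.02508 at 3:2, about 5.7% higher (SE about 2.8% higher). No figure includes a cluster-crossover effect, because the protocol gives no intracluster correlation.

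**6. Concurrent periods.** Let a, b and c be the shares of two-week periods with both clusters on ETI, both on SGA, and on opposite devices. Then a + c/2 = 0.6 and b + c/2 = 0.4, so a − b = 0.2 and a is at least 0.2. However the sequence is drawn, at least 20% of periods have no concurrent SGA patients.

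**The case against.** The best defence is that section 4.5 speaks of the final analysis without saying ITT, and section 9 also plans an as-treated analysis. Balancing treatment actually delivered is a coherent aim, and 3:2 does serve it better than 1:1. With half of failures rescued with the other device, as-treated is 324:409 under 3:2. Under 1:1 it would be 255.6 + 0.5 × 42.6 = 277 against 383.4 + 0.5 × 170.4 = 469. This stands as a reason why the sponsor may want 3:2. It does not rescue the promise, because as-treated balance depends on a rescue mix that the protocol does not fix.

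It is also fair to say that unequal allocation is legitimate, that it does not bias ITT, and that the split rests on equal accrual per cluster-period.

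A reader might infer more than the documents support:

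- *That the real comparison is among first-attempt successes.* No section plans such an analysis; the arms are defined by the primary device assigned, and section 9 commits to ITT.
- *That the arms are not compared concurrently.* Only a minimum of 20% of periods is forced to be ETI-only; up to 80% can have the clusters on opposite devices. The rest is a matter of scheduling. With independently randomised clusters, opposite-device periods would be 2 × 0.6 × 0.4 = 48% at 3:2 and 50% at 1:1. Each cluster also crosses over between periods.
- *That the ratio explains the weak power.* At 1:1 the shortfall is already 1,530 − 852 = 678 patients; the ratio adds about 73.

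**Conclusion.** The point holds as an incorrect design statement with a small statistical cost. The 3:2 ratio equalises expected first-attempt successes, about 307 each. The balance claimed in section 4.5 is wrong for ITT, where about 511:341 is expected, and not guaranteed as-treated, where the range under a common rescue share is about 307:307 to 341:511.

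Under ITT, power at 852 is about 2 points lower than at 1:1, and about 73 more patients would be needed for 80% power, before any cluster effect. At least one two-week period in five has no concurrent SGA comparator.

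These sizes rest on equal accrual per cluster-period, on the section 5 rates, and, for the as-treated range, on classifying patients by the device finally in place. The imbalance is an expectation, though a chance return to equality is very unlikely. The documents do not show that ITT is biased or that the 3:2 schedule has to be abandoned.

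**What to change.** In section 4.5, replace the claim of balance in the final analysis with a statement that 3:2 is chosen to equalise expected first-attempt successes, and that about 511 ETI and 341 SGA patients are expected under ITT if accrual per period is equal. In section 5, state the allocation ratio and base the power on that split. This costs two short edits and a recalculation, and leaves the running schedule alone.

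If allocation has not started, the sponsor may consider 1:1 periods with the two clusters always on opposite devices and the order randomised. That gives every period a concurrent comparator and recovers the small loss of precision. It needs a new schedule from the study center. It also makes first-attempt successes less even (426 × 0.6 = 256 vs 426 × 0.9 = 383) and widens the as-treated imbalance. It is a trade-off for the sponsor, not a necessary correction.

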#### **4.6. Exposure management**

##### **4.6.1. Intervention group**

The intervention arm of the trial is primary ETI in eligible patients according to inclusion criteria. The endotracheal tube will be inserted via direct laryngoscopy but

not video laryngoscopy. There is no additional training course for paramedics who are involved in this trial.

The confirmation of success ETI is mainly by end-tidal capnographic data and auscultation. Protocol-based single-attempt intubation is also applied.

If the first advanced airway attempt fails, rescue airway management including SGA insertion or BVM ventilation are allowed.

#### **4.6.2. Control group**

The control arm of the trial is primary SGA insertion in eligible patients according to inclusion criteria. The SGA which is used in the trial is second-generation supraglottic airway device from Intersurgical (i.e., i-gel). There is no additional training course for paramedics who are involved in this trial. Misplacement of SGA is less common due to its design to create an anatomical seal of the pharyngeal, laryngeal and perilaryngeal structures. Protocol-based single-attempt SGA insertion is also applied. If the first advanced airway attempt fails, rescue airway management including ETI or BVM ventilation are allowed.

### **4.7. Outcomes measurement**

#### **4.7.1. Primary outcome:**

The primary outcome of the trial is sustained ROSC (defined as ROSC  $\geq 2$  h). Due to overcrowded condition in Taiwan's emergency departments, patient's admission could be delayed. Therefore, sustained ROSC was used and was well-validated in previous study in Taiwan. [14]

#### **4.7.2. Secondary outcomes:**

The following secondary outcomes will be analyzed during the trial: prehospital ROSC, survival to hospital discharge, favorable neurological outcome (defined as cerebral performance category scores 1 and 2, CPC  $\leq 2$ ).

### **5. Sample size estimation**

The sample size estimation is based on the primary outcome of sustained ROSC. According to previous study conducted in Taipei, sustained ROSC rate was 24.4% for SGA and 30.8 % for ETI. [15]

We estimated to enroll 852 patients to detect the absolute difference of 6.4% between the SGA and ETI group to have 80% power and a two-sided  $\alpha$ -level of 0.05.

Considering the number of OHCA patients treated by the participating ALS teams in Taipei is about 300 patients annually, we expect to have adequate number of patients of the three years study period.

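### 852 patients give about 53–55% power for 24.4% versus 30.8%, not the stated 80%; about 1,530–1,602 patients would be needed

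*Protocol*

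**What the plan says.** Section 5 rests the calculation on the primary outcome: "The sample size estimation is based on the primary outcome of sustained ROSC". It takes both rates from an earlier Taipei study: "sustained ROSC rate was 24.4% for SGA and 30.8 % for ETI". From these it concludes: "We estimated to enroll 852 patients to detect the absolute difference of 6.4% between the SGA and ETI group to have 80% power", at a two-sided significance level of 0.05. It then notes that the participating teams treat about 300 OHCA patients a year and expects three years to bring in enough of them.

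Section 2 repeats the number, "we estimated the sample size as 852 patients of OHCA to detect the primary outcome difference", and allows 34 months for enrolment.

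Section 4.5 allocates "three periods of ETI to two periods of SGA (3:2 ratio"). Its stated purpose is: "To guarantee a balanced case number in the final analysis". Section 4 describes cluster randomization with periodic crossover. Section 5 mentions no dropout rate, intracluster correlation, design effect or adjustment for interim analyses.

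**The concern.** A comparison of roughly one quarter with just under one third, at 80% power and a two-sided 5% level, ordinarily needs well over a thousand patients. A total of 852 looked too small by nearly half, and every input needed to check it is printed in the same section.

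If the total is too small for the stated difference, the headline claim about the primary outcome is wrong. Readers who trust the 80% would give a non-significant result more weight against a 6.4-point benefit than it can bear. The recruitment forecast would fail with it, because it is judged against the wrong target.

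**Working it through.** **Inputs (Section 5 unless noted).** p1 = 0.244 (SGA); p2 = 0.308 (ETI); d = 0.064; two-sided alpha 0.05 (z = 1.960); power 80% (z = 0.842); N = 852. Section 4.5 gives 3:2 for allocation periods but aims at balanced case numbers, so both 1:1 and 3:2 patient splits are shown.

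**1. What reproduces.** The difference does: 30.8 − 24.4 = 6.4 points. So does the enrolment period: 300 × 34/12 = 850 patients. The 852 is therefore the whole trial.

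**2. Required size at 1:1 (pooled-variance formula).**

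n per arm = [1.960 × √(2 p̄(1 − p̄)) + 0.842 × √(p1(1 − p1) + p2(1 − p2))]² / d², with p̄ = 0.276.

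- First term: 1.960 × √0.39965 = 1.2390
- Second term: 0.842 × √(0.18446 + 0.21314) = 0.5307
- n = (1.7697)² / 0.004096 = 764.6, so 765 per arm and **1,530 in total**

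**3. Required size at 3:2 (ETI:SGA).** The same formula with r = 1.5 and p̄ = (0.244 + 1.5 × 0.308)/2.5 = 0.2824 gives 640.7 SGA patients. The total is 2.5 × 640.7 = **1,602** (1,603 if each arm is rounded up).

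**4. Power with 852 patients.** Power = Φ[(d − 1.960 × SE0)/SE1], where SE0 uses the pooled rate and SE1 the separate rates.

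| Split (SGA/ETI) | SE0 | SE1 | Power |
|---|---|---|---|
| 426/426 | 0.03063 | 0.03055 | Φ(0.130) = **55.2%** |
| 341/511 | 0.03148 | 0.03095 | Φ(0.074) = **53.0%** |

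**5. Detectable difference.** With SGA fixed at 24.4% and N = 852, 80% power is reached at 8.7 points (1:1) or 8.9 points (3:2), an ETI rate of about 33%.

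**6. Search for a reading that gives 852 at 80% power.**

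| Variant | Total N at 80% power |
|---|---|
| Unpooled, 1:1 | 1,524 |
| Arcsine, 1:1 | 1,527 |
| Log odds ratio, 1:1 | 1,537 |
| Continuity-corrected, 1:1 / 3:2 | 1,592 / 1,668 |
| One-sided 0.05, all variants | 1,200 to 1,325 |

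None comes near 852. A one-sided test with 852 patients would have only 65–67% power, and Sections 5 and 9 both specify two-sided tests. Taken as 852 per arm, power would be 84%.

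**7. Recruitment.** At 300 a year, 1,530 patients take 5.1 years and 1,602 take 5.3 years. Three years bring about 900.

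**The case against.** **852 may be a per-arm number.** The nearest route is 765 per arm inflated for 10% dropout: 765/0.9 = 850. But no dropout rate is stated, and Sections 2 and 5 both use 852 as the trial total. At most this suggests how the slip arose.

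**The 3:2 ratio applies to periods.** This is fair. The stated aim is balance, so the patient split may be near 1:1 in an as-treated analysis. It moves power only between 53% and 55%.

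**The design is cluster-crossover with interim analyses.** The true requirement could differ from the figures here. The protocol gives no correlation from which to work this out, and it claims no efficiency gain that could justify 852. The point stands as a caveat on the corrected figures, not as a defence of the stated one.

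**Confidence intervals are already planned.** Section 9.1 does commit to them, so misreading a null result is a risk and not something the protocol proposes. The stated power is wrong all the same.

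**Three years at 300 a year do cover 852.** True. The adequacy statement fails only because 852 is the wrong target, so it is a consequence and not a second error.

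**Failed first attempts might dilute the contrast further.** This depends on an assumption. If the 24.4% and 30.8% are rates by device actually used, the 60% and 90% first-attempt success in Section 4.5 would shrink the intention-to-treat difference to between 6.4 × (0.60 − 0.10) = 3.2 and 6.4 × 0.60 = 3.8 points, with power of about 18–24%. The protocol does not say how those rates were classified, and it also allows bag-valve-mask rescue, for which it gives no rate. The conclusion does not rely on this.

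**Conclusion.** The concern holds. On the protocol's own rates, significance level and total, power is 53–55% and not 80%, a shortfall of about 25 percentage points. Reaching 80% for 6.4 points needs about 1,530 (1:1) to 1,602 (3:2) patients, some 1.8 to 1.9 times the planned number. The finding does not depend on the choice of formula, the sidedness of the test or the allocation ratio. The figures treat patients as independent and allow for no interim looks. The document cannot show whether the rates, the power or the sample size was the element entered wrongly. It does show that they cannot all be right.

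**What to change.** First retrieve the original calculation and establish which element is in error. If the rates stand, keep the 852-patient, 34-month trial and correct the text:

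- **Sections 2 and 5:** state that 852 patients give about 55% power at a 1:1 patient split, or 53% at 3:2, for 24.4% versus 30.8%. Equivalently, they give 80% power for about 8.7–8.9 points (24.4% versus about 33%). Say which split is assumed, and that the figures assume independent patients and no interim analyses.
- **Section 5:** remove the statement that three years are adequate for a 6.4-point difference.
- **Section 9.1:** add that a non-significant result does not by itself exclude a 6.4-point difference, and that the result will be interpreted from the confidence interval. With 852 patients the 95% half-width is about 6 points on the difference scale (1.96 × 0.0306 = 0.060).

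The cost is protocol wording and a less favourable power statement, with no extra patients or time. Keeping the 80% claim for 6.4 points would instead mean enrolling about 1,530–1,602 patients, which at the stated rate takes more than five years.
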